### Data handling and record keeping

The personal details of each participant will be collected and stored digitally in a database. Data managers will manage and monitor the data to analyse abnormal values and missing data. The database will be locked after data collection. To ensure data completeness and accuracy, the locked database will be provided to the statistician, who is not a part of the study team and will conduct independent statistical analyses. The data will be stored in a locked place for 5 years.

### Ethical considerations, amendments and dissemination

This trial will be conducted in accordance with the Declaration of Helsinki. The informed consent and assent process is in line with the Good Clinical Practice guidelines. This study plan (protocol version 1.2) is approved by the ethics committee of Beijing Friendship Hospital, Capital Medical University, China (2022-P2-051–02). Any significant modifications, which may affect the study and potential benefits or safety of the patients, including the changes in study objectives, study design, patient population, sample sizes, study procedures, and significant administrative aspects, made in the study protocol or other study documents will be submitted to the local medical ethical committee for approval and require a formal amendment. All the study participants will be notified, and informed consent will be requested again when necessary. The amendment will be updated on the trial register website to ensure transparency. The results of this trial will be published in a scientific journal or presented at scientific conferences, regardless of the outcome.

## Trial status

The recruitment will start on October 1, 2022, and is expected to be completed on April 1, 2023.The trial will start recruiting the patients in the Beijing Friendship hospital, Capital Medical University. Recruitment at other centres will begin when ethical approval is available.

## Discussion

In recent years, for sedation, propofol combined with an analgesic has replaced its conventionally utilised combination with benzodiazepines and has become the standard for analgo-sedation for upper GI endoscopy with the advantages of improved sedation titration, short recovery time, and good patient tolerance and satisfaction. Esketamine offers the advantage of the minimisation of sedation side effects, making optimal use of the synergy concept while acting as an analgesic. Susanne Eberl et al. reported that the use of esketamine in patients during ERCP resulted in good sedation and analgesia quality [13]. However, some main questions remain unanswered. What are the optimal dose and drug compatibility recommended in clinical use? What is the efficacy of esketamine on tussis inhibition? What is the effectiveness of esketamine in the Chinese population? Can esketamine be well tolerated in actual clinical practice? Esketamine is the first esketamine biosimilar developed in China. Phase III studies in China have shown that esketamine with a shorter recovery and orientation recovery times than esketamine presents potential clinical advantages [16, 17]. Although its pharmacokinetics and safety have been reported preliminarily, the data were only from small-scale studies. Moreover, safety analyses in a clinical setting are limited. Therefore, we selected the RCT (randomised controlled trial) for numerous cases to explore the efficacy and safety of esketamine to obtain highly reliable evidence for the clinical application and risk management of esketamine.

Propofol is one of the most common drugs used in gastrointestinal endoscopy [18]. Compared with midazolam/pethidine, propofol has faster sedation induction and shorter half-life, and its use is increasing every year [19, 20]. Although propofol has its advantages, it has no analgesic effect. In addition, propofol sedation can easily provide a higher dose of general anaesthesia. Moreover, propofol is associated with circulatory and respiratory suppression, particularly in elderly patients [21, 22]. The combination of propofol and opioids is a commonly used anaesthesia method in bronchoscopy, although it is known that there are hypoxemia, postoperative nausea, and vomiting and other side effects, especially for patients without airway devices [23, 24]. Joskova et al. found in animal experiments that the pharmacological interaction between propofol, sufentanil, and midazolam mediated by GABAA receptors has a negative impact on the ciliary pulsation frequency of respiratory epithelial cells [25]. The affinity of s-enantiomer esketamine of ketamine racemic mixture to NMDA receptor is higher than that of r-enantiomer. Jiangsu Hengrui Medicine Co., Ltd., completed the preclinical study of Esquitan 3 years ago and obtained the clinical study approval from the State Food and Drug Administration [16]. Esketamine has sedative and analgesic functions. In addition, its sympathetic nervous system-like properties offset the hemodynamic inhibition of propofol, thereby reducing the risk of cardiovascular and respiratory depression. Hypotension is uncommon due to the increased tension of sympathetic nervous system and the maintenance of spontaneous breathing and airway reflex [26]. The combination of local pharyngeal anaesthetic (TPA) and intravenous sedatives may be helpful for endoscopic examination and improve the tolerance of patients by reducing vomiting reflex. Although the efficacy of adding TPA in intravenous sedation is still controversial, data from a clinical trials have examined the combination of lidocaine and propofol and showed that the use of lidocaine in conjunction with propofol during elective EGD might delay the time to discharge of patients. Given the fact that esketamine, sufentanil, or lidocaine combined with propofol showed better clinical outcomes, we recruited 400 patients and stratified them according to the operation type and age to acquire large-scale, randomised evidence for the safety and effectiveness to reduce the cough reflex of esketamine. Currently, American Society of Anesthesiologists (ASA) classification I–III will be randomised to four groups: P group (single administration of propofol), P + S group (administration of propofol and sufentanil in combination), P + K group (administration of propofol and esketamine in combination), and P + L group (administration of propofol and lidocaine in combination) (*N* = 100 per group). By this study design, the efficacy of these combinations will be evaluated.

In this trial, we plan to recruit 400 patients and stratified them according to the operation type and age to acquire large-scale, randomised evidence for the safety and effectiveness to reduce the cough reflex of esketamine.

Although the trial is designed carefully, some limitations remain persistent. First, we designed this RCT with the inherent limitation, the potentialcriticism for increased resources. Second, maybe the sample cannot exhibit good typicality due to theconcentrationofcasesinBeijing3Agradehospitals.Moreover, the questionnaires, which may be influenced by the patient’s perception of pain, are highly subjective; therefore, theymaynotdirectlyprovidetheeffect and lead to subjective bias. Thus, before beginning the trial, the investigator and site staff will receive systemic training for theuseofthequestionnairesand be certificated to prevent subjective bias to the highest possible extent.

In summary, this trial will be an important attempt to evaluate the efficacy and safety of esketamine in upper GI endoscopy. Moreover, in a large population and real settings, the proposed approach can be completely qualified for the selection of the optimal treatment for sedation in upper GI endoscopy.

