## Methods and analysis

### Study design

This paper presents a prospective, randomised, controlled, three-blind, two-centre study registered in the Chinese Clinical Trial Registration Center. The trial will be conducted at Beijing Friendship Hospital and Beijing Tian Tan Hospital, Capital Medical University, China. We have used the SPIRIT reporting guidelines and completed SPIRIT checklist (Additional file 2). Hence, this study enrolled 400 patients (200 patients per centre) from October 2022 to April 2023. Before the study starts, all the staff took a course so they can explain more clearly to the patients, which helped us to get enough participants. The random sequence generator of STATA MP 14 software generated random numbers and divided them into four groups. Patients will be randomly divided into four groups in the ratio of 1:1:1:1. For each selected patient, the researchers drew an envelope to determine their grouping, but the patients were not informed of the grouping. Except for propofol, clinical researchers injected transparent solution into the syringe in random order in the same bottle containing the code. The researchers who conducted randomisation and blinding procedures did not participate in subsequent studies. Other researchers were not informed about the grouping of research and experimental drugs. To ensure the concealment of the allocation, the randomisation results were sealed until the end of the study. The trial auditing process was conducted by an independent team. Whether a centre underwent a monitoring or auditing visit was determined based on scheduling and availability of the auditor, their proximity to each site, and site convenience. We sometimes scheduled the timing of auditing visits for new research staff or following site initiation visits for a different trial led by the Methods Center to reduce travel-related costs. Auditing was conducted in-person.

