### Randomisation and blinding

Randomisation will be performed as follows. Based on different study centres (two groups), the patients will be classified into four groups: P group (single administration of propofol), P + S group (administration of propofol and sufentanil in combination), P + K group (administration of propofol and esketamine in combination), and P + L group (administration of propofol and lidocaine in combination) (*N* = 100 per group). The random sequence generator of the STATA MP 14 software generated random numbers and divided them into four groups. Only the nurse (A) who is responsible for preparing the trial drug knows the grouping information automatically generated by a computer. She (A) will generate the allocation sequence. The chief anaesthesiologist (B) will enrol patients and assign participants to interventions. Computer-generated random grouping numbers will be printed and placed in separate sealed envelopes. After meeting a participant who meets the inclusion criteria, the anaesthesiologist will assign the newly recruited participant to a group according to the number provided in the envelope. Both the anaesthesiologists and patients are unaware of the treatment plan. Anaesthetic drugs will be prepared and labelled with numbers by nurses and injected by the anaesthesiologists. The anaesthesiologists will record the physiological characteristics of each patient. In emergencies, the nurses can provide the anaesthesiologists the information of drugs to ensure clinical safety. The designed blinding method is as follows: This study will use the three-blind method to ensure the objective evaluation of results. The preoperative preparation of anaesthetic drugs, anaesthesia implementation for upper GI endoscopy, and PACU (postanaesthesia care unit) clinical data collection and follow-up after the operation will be performed by three medical personnel to ensure that pharmaceutist, operators, recorders, and the patients are blind to group classification. On the day of study, an envelope with the smallest sequential number was opened first and the solutions of medicines were prepared in a syringe by an investigator based on the number appeared on the paper slip. Then, the unlabelled syringes of solutions were handed over to an anaesthesiologist who was performing general anaesthesia and administrating the medicines but was blind to the contents inside of the syringes. Another anaesthesiologist who observed and recorded the data intraoperatively and postoperatively was also blinded to the medication patient had received. All sedation procedures were standardised and performed by the same anaesthesiologist who was blind to the patient groups. PACU (postanaesthesia care unit) clinical data collection and follow-up after the operation were also blinded to the therapeutic regimen. The allocation sequence was not available to any member of the research team until databases had been completed and locked. An agreement from PI will allow unblinding of individual participants on a need-to-know basis and, if necessary, termination of treatment in the event the MSO and investigator determine the participant has had a serious adverse reaction to the study medication. Emergency unblinding can be performed at any time if it is considered necessary by the principal investigator. Participants are issued with “In case of emergency” cards to be carried at all times during the study including an emergency phone number. If the trial or a single subject is prematurely unblinded, the principal investigator will document the reason for unblinding and notify the ethics committee. Unblinding of the project statistician who will analyse the data will occur at the end of the study, after the last participant has been evaluated, all data have been entered and cleaned, and the database has been locked.

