### Statistical methodology

Efficacy assessment is based on the intention-to-treat (ITT) population, which is defined as all randomised patients. Safety analyses will be performed in a safety evaluation set, which is a subset of all the patients exposed to a minimum of one dose of the studied medication. The SPSS 24.0 software will be used for statistical analyses. Significance will be analysed using two-sided tests, and *p* < 0.05 will be judged as the statistical significance standard. The normally distributed measurement data are presented as mean ± standard deviation (*x* ± *s*). The quartile method will be used to explain the measurement data with non-normal distribution. The repeated analysis of variance and Turkey test will be used for comparisons within a group and between multiple groups, respectively. Count data will be analysed using non-parametric tests, such as Rank-sum test, chi square test, and Fisher exact test. The multivariate regression analysis will be employed to explore the effects of different analgesic drugs combined with propofol on tussis during upper GI endoscopy. We will consider performing predefined subgroup analyses on the primary endpoints according to age, operation types, and special populations. Missing data will not be imputed. In addition, the primary endpoint analysis will also be conducted in a per-protocol set and compared with the ITT analysis to analyse sensitivity. No interim analyses are planned.

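### The allocation factors are stated inconsistently (centre in one section, operation type and age in another), and the planned tussis analysis is not tied to whichever factors were used

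*Protocol article*

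**What the plan says.** Allocation is described in three places in the protocol article.

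- Randomisation and blinding: "Based on different study centres (two groups), the patients will be classified into four groups". No other factor is named. Study design adds the split by centre: "this study enrolled 400 patients (200 patients per centre".
- Discussion, paragraph on propofol and its combinations: "we recruited 400 patients and stratified them according to the operation type and age".
- Discussion, just before the limitations: "we plan to recruit 400 patients and stratified them according to the operation type and age". Neither Discussion sentence mentions centre.

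For analysis, Statistical methodology says: "Count data will be analysed using non-parametric tests, such as Rank-sum test, chi square test, and Fisher exact test". For measurement data it says: "The repeated analysis of variance and Turkey test will be used for comparisons within a group and between multiple groups, respectively". Tussis also gets a model: "The multivariate regression analysis will be employed to explore the effects of different analgesic drugs combined with propofol on tussis during upper GI endoscopy". No covariates are listed for it. Age and operation type appear in that section only as subgroup factors that the authors will consider. On incomplete data: "Missing data will not be imputed". The Endpoints section lists nine post-procedure times, from 0.5 h to 6 months, for MMSE, MET and sleep. The Assessments section has MMSE measured before the procedure.

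**The concern.** A reader cannot tell from the article which factors the allocation list was built on. That matters because the analysis should follow the allocation. When arms are balanced within levels of a factor that predicts the outcome, the balance removes part of the chance variation between arms. A test that ignores the factor still counts that variation in its standard error. Its p-values are then too large and its intervals too wide, and some power is given away for nothing.

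The chi-square, Fisher and rank-sum tests have no place for centre, age or operation type. The regression could carry them, but it is offered only as exploration and is not connected to the allocation.

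A separate and smaller issue concerns the repeated scores. Standard repeated-measures ANOVA uses only patients with every visit present. With nine times, follow-up by phone to 6 months and no imputation, any patient with one missed visit drops out of that analysis. This fits poorly with an efficacy population defined as all randomised patients.

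**Working it through.** **Plan figure to reproduce.** There is none on this point. The article gives no tussis rate under propofol alone and nothing on how strongly centre, age or operation type predict tussis. The rates below are assumptions, shown as a range.

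**Inputs**
- From the article: 200 patients per centre, four arms 1:1:1:1, so 200/4 = 50 per arm per centre. The 10% loss in Sample size calculation leaves 45. Tests are two-sided at 0.05.
- Assumed: one comparison, propofol alone against propofol plus esketamine; common odds ratio 0.41, which takes 30% to about 15%; arms balanced within centre; centre control rates as shown.

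**Step 1. Type I error in closed form.** With arms balanced within two equal centres, the unstratified test uses variance p(1−p) at the pooled rate p. The true variance is the mean of the within-centre values p_c(1−p_c). The standard error is too large by r = √[p(1−p) / mean p_c(1−p_c)], and the actual two-sided error is 2[1 − Φ(1.96r)].

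- 20%/40%: p = 0.30, so 0.21. Within centre: (0.16 + 0.24)/2 = 0.20. r = √(0.21/0.20) = 1.025. Error = 2[1 − Φ(2.008)] = 4.5%.
- 15%/45%: again 0.21. Within centre: (0.1275 + 0.2475)/2 = 0.1875. r = 1.058. Error = 2[1 − Φ(2.074)] = 3.8%.

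**Step 2. Simulation** (200,000 trials per setting, 45 per arm per centre): unstratified chi-square against Cochran-Mantel-Haenszel (CMH).

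| Centre control rates | Type I, unstratified | Type I, CMH | Power, unstratified | Power, CMH |
|---|---|---|---|---|
| 30%/30% | 5.0% | 5.0% | 0.68 | 0.68 |
| 25%/35% | 4.8% | 5.0% | 0.68 | 0.68 |
| 20%/40% | 4.4% | 4.9% | 0.66 | 0.67 |
| 15%/45% | 3.8% | 5.0% | 0.62 | 0.66 |

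The simulated type I errors agree with step 1.

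**Step 3. More strata.** A second simulation (20,000 runs) used 100 per arm and eight strata balanced by arm. Rates were 30% against 15% overall, and stratum log-odds were spread evenly over ±s.

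| s | Type I, unstratified | Power, unstratified | Power, stratified |
|---|---|---|---|
| 0 | 5.3% | 0.73 | 0.73 |
| 1 | 4.1% | 0.73 | 0.74 |
| 1.5 | 3.5% | 0.74 | 0.78 |
| 2 | 2.6% | 0.74 | 0.81 |

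**Step 4. Factors not used in allocation.** When allocation is not stratified by centre, the unstratified chi-square keeps its level: 5.0% at 20%/40% and 5.1% at 15%/45% (40,000 runs). Leaving out a factor that was not used in allocation does not distort the standard error.

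**Step 5. Repeated scores.** If a share m of patients misses each visit independently, (1−m)^9 have all nine. At m = 3% that is 76%, and at 5% it is 63%. Both values of m, and the independence, are assumptions. If the 10% loss in the sample size section were all dropout, with no other missed visits, about 90% would be complete.

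**The case against.** The strongest reply has four parts, and much of it stands.

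1. **The statements may be compatible.** One list can be stratified by centre, age and operation type together. The Discussion says that patients are stratified, not that the allocation is, and may mean the subgroups in Statistical methodology. A reader might infer two incompatible lists, but the text does not prove that. The need to clarify remains: the section that defines the allocation names only centre, and both Discussion sentences link the stratification to randomised evidence.
2. **No primary test is designated.** The count-data list is introduced as examples, and the only method tied to tussis is the regression, which could carry all these factors. So a reader might infer that the primary analysis is an unstratified chi-square, but the article does not say so. An analysis plan may also settle the covariates. What stands is that the article names unstratified tests and presents the regression as exploratory.
3. **The loss may be nil.** It needs allocation balanced on a factor that predicts tussis. Two hospitals of the same grade in one city with standardised sedation may differ little. Assuming control rates of 10% and 60% gives about 10 points of power lost, but nothing in the article suggests such a gap, and that setting represents 35% falling to 21%, not 30% to 15%.
4. **The ANOVA sentence covers both comparisons.** It gives repeated ANOVA to within-group and Tukey to between-group comparisons, so it would be wrong to say that the drugs are never compared. It does not name MMSE or MET, and vital signs are repeated data too. Declining to impute is also not the same as specifying complete-case deletion; a mixed model does not impute either.

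**Conclusion.** The point holds as an unresolved inconsistency with a conditional, modest cost. The article should state one set of allocation factors, and the tussis comparison should adjust for them. If allocation was balanced within factors that predict tussis, ignoring them is conservative. Under assumed centre rates from 20%/40% to 15%/45%, type I error is about 4.4% to 3.8% and roughly 1 to 4 points of power are lost. With more and stronger strata (s = 2) the loss reaches 7 points; with weak strata it is close to zero.

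A reader might conclude that the error bars are wrong whichever description is true, or that false positives are a risk. Neither follows: the error runs in the cautious direction, and it arises only for factors actually used in allocation.

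On the repeated scores, the complete-case drawback of standard repeated ANOVA is real if that method is applied to them. Its size is not given by the article, so 76% and 63% are illustrations and not estimates.

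**What to change.** 1. State the factors used to build the allocation list, in the same words in Randomisation and blinding and in the Discussion. If the Discussion means subgroups, say so.
2. Make the primary tussis comparison a Cochran-Mantel-Haenszel test stratified by those factors (at least centre), or a logistic regression of tussis on arm and those factors, with an adjusted risk difference. If age and operation type were not used in allocation, enter them as prespecified covariates.
3. For MMSE and MET over the nine times, replace repeated ANOVA and Tukey with a linear mixed model containing arm, time, arm-by-time and centre, plus the baseline score where it is collected (MMSE), fitted to all available visits.

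The cost is wording and slightly more programming, with no new data and no extra patients. In the two-centre settings examined, the stratified test kept its 5% level and lost no power.
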